# STUDY PROCEDURES

1. **Recruitment of participants**

All residents and care staff who meet the selection criteria will be eligible to participate in this study. They will be identified by the Nursing Unit Managers (NUM) and the speech pathologist/s at Maroba Aged Care and provided with an information flyer (Resident Information Flyer, Appendix O. Care Staff Information Flyer, Appendix P). The residents/families of residents/care staff will be provided with a participant information statement (Residents, Appendix Q. Care staff, Appendix R) regarding the study, and then followed up by the NUM/speech pathologist for interest in study participation. There will be an opportunity for residents, family of residents, and care staff to ask questions before and after consenting to participation. Questions regarding the study can be directed by the staff at Maroba Aged care to the Principal Investigator. Residents/family of residents/care staff will be required to sign and provide written consent for participation (Residents, Appendix S. Care staff, Appendix T). Consideration and return of consent for participation in the study will be 7 days after initial contact.

Explanation will be provided to residents/family of residents that their usual oral health care and dysphagia treatment will not vary with or without participation in this study. Further to this, a statement will be provided to participants that based on the results of the pilot study, the larger clinical trial may not be performed.

This research will involve the use of information without personal identifiers and it will be obtained from individuals or gathered from medical files by care staff appointed by Maroba Aged Care. The existing data information seen in section 9d. will be collected for each consented resident.

As this is a feasibility study utilising a myofunctional device not previously trialled in this setting, all consented residents will receive the treatment intervention to better understand acceptability of the device and feasibility of completing a larger trial. No randomisation of participants will occur. The number of participants that will be aimed for recruitment – up to 50 residents and 10 staff. This is based on the available recruitment pool, and the number of residents who may not give consent. Because this is a feasibility study this does not require sample size base.

The period of time for expected time to recruit participants is four weeks.

1. **Study procedures**

Staff:

Education will be provided before the commencement of the trial intervention by the principal investigator from the University of Newcastle to care staff, regarding familiarization and instructions for use of the myofunctional device (MyoMunchee
[figure not shown]
), cleaning and storage of the device, and documentation of device use.

The use of a myofunctional device (MyoMunchee
[figure not shown]
) will be required for each participant for the duration of this intervention and will be provided in kind by MyoMunchee
[figure not shown]
. Further explanation regarding the cleaning, cleaning schedule and storage of this will be provided in the treatment protocol as per MyoMunchee
[figure not shown]
 cleaning protocol.

The research team will provide the residents/care staff with instructions and a guide for the use of the device. This will require active use of the device with the action of chewing.

The use of the myofunctional device will be monitored by the care staff at Maroba Aged Care, with documentation on a daily checklist provided for each participant. The daily checklist will be collected by the care staff at Maroba Aged Care at the end of each week of intervention and entered into an electronic database each week by the principal investigator.

Following the five week intervention, the care staff will be asked to complete a questionnaire regarding acceptability and feasibility of the trial intervention.

Residents:

Once participants who meet the selection criteria are enrolled in the study, outcome measures will be collected and stored by the principal investigator from the University of Newcastle. The collection of outcome measure should take approximately 60 minutes for each participant.

There will not be any alteration to the participant’s usual intervention for oral care or swallowing treatment unless this is deemed appropriate by the usual treating speech pathologist/s at Maroba Aged Care, or the treating medical/nursing team.

The trial intervention using the myofunctional device will commence within two weeks post pre-treatment outcome measure collection.

The myofunctional device (MyoMunchee
[figure not shown]
) will be used twice daily (morning and evening recommended at the time of usual oral care routine) by the participants. The duration for device use will start at 1 minute twice a day in the first week, and increase to 2 minutes twice a day in the second week, 3 minutes twice a day in the third week, 4 minutes twice a day in the fourth week, and 5 minutes twice a day use in the fifth week of intervention.

Following the five week trial of intervention, post-treatment outcome measures will be taken by the lead researcher from the University of Newcastle.

Post treatment intervention, residents will be asked to take part in a survey regarding the acceptability of the myofunctional devices.

Protocol Flow:

1. **Methods of data collection**

Data collection will be completed by a qualified clinical speech pathologist/principal investigator (with over 17 years clinical experience) with reliability checking of 10% of residents onsite at Maroba Aged Care by a qualified clinical speech pathologist from the University of Newcastle.

Pre and post treatment outcome measures will be taken for comparison, along with data collected for adherence to treatment by way of daily checklist completion by the care staff, which will be collected at the end of each week and stored by the research team for the duration of the trial. Further to this a survey of the residents completing the intervention, as well as a questionnaire for the care staff assisting participants with the intervention will be taken at the completion of the five week intervention trial.

1. **Access to Existing Data**

Data (as per the form below) will be extracted from the medical files of each consenting participant by an employee appointed by Maroba Aged Care. The data will be deidentified using a code and then provided to the research team.

| **Name/Description of data** | **Myofunctional Devices Research** | | | | |
| --- | --- | --- | --- | --- | --- |
| **Data Custodian** | University of Newcastle | | | | |
| **Agency Type** | Higher Education | | | | |
| **Data Collection Format** | Non-identifiable | | | | |
| ***Variable*** | ***Justification*** | | | | |
| **Resident ID number** |  | | | | |
| **Male/Female/Non-binary** |  | | | | |
| **Date of Birth/age** |  | | | | |
| **Identifies as Aboriginal or Torres Strait Islander** | Yes/No | | | | |
| **Underlying Medical Diagnosis** | - CVA– year _________________ - Dementia - Parkinson’s Disease - Cardiovascular disease - Cancer – specify _____________ - COPD - Diabetes - Multiple Sclerosis - Epilepsy | | | - Hypertension - Osteoporosis - Arthritis - Depression - Asthma - Motor Neuron Disorder - Polymyositis - Other_______________________   ___________________________ | |
| **Dentition (own, edentulous, dentures)** | Own/Dentures/Edentulous | | | | |
| **Diet/Fluid consistency** | - NBM - PEG - JJ Tube - Other _________ | - Liquidized - Puree - Minced Moist - Soft Bite Sized - Easy Chew - Normal Diet | | | - Extremely Thick - Moderately Thick - Mildly Thick - Slightly Thick - Thin fluids |
| **MMSE score/date last assessment** | Score: | | Date: | | |
| **Independence in oral care** | Yes/no/maybe/unsure | | | | |
| **Living status** | Independent living/ACF (check terminology) | | | | |

1. **Safety considerations**

This study involves a new intervention with a vulnerable population. However, the intervention uses a device that has Therapeutic Goods Approval and the residents who will be using this device will be monitored by care staff during the intervention.

Potential Risks and Solutions for residents undertaking intervention

| **Potential Risks** | **Solutions** |
| --- | --- |
| Aspiration of saliva secondary to increased saliva production during device use | Aspiration of saliva occurs daily. The continued use of usual oral care during this study to ensure adequate oral hygiene should assist with reducing complications that may arise from aspiration of saliva  Monitoring by care staff to ensure participants have adequate salvia management/control  If coughing occurs through use of the device and increased saliva production, a referral will be made for speech pathology at Maroba to review swallowing function (and appropriateness for continuation in study) |
| Initial discomfort to gums/jaw with the action of chewing the device | The treatment intervention has been staged in time use of the device, increasing weekly to allow for adjustment to oral comfort. If oral discomfort is identified/reported, a review by the researcher and speech pathologist at Maroba Aged care will take place and recommendations will be made for continuation in the study.  Sizing and selection of the device has been considered for oral comfort and ease placing and removing the device from the oral cavity with an eternal tab/handle. |
| Infection control | Infection control procedures are outlined in the treatment manual and are consistent with Covid 19 safety and cleaning measures. Staff will be trained in cleaning protocols for the device (which are not aerosol generated) to reduce the risk of infection. Daily cleaning will be tracked with the completion of a daily check list by care staff at the ACF. |

The risks to the participants undertaking intervention is considered negligible to low risk. There is low foreseeable risk of harm or discomfort, and any foreseeable risk is no more than an inconvenience (National Statement on Ethical Conduct in Human Research, 2007).

There are no known risks for the care staff assisting with the intervention outside of usual oral care assistance.

Further considerations have been made below not specifically to risk, but rather in regard to storage and labelling, which may impact on infection control for the use of the device.

Device considerations and storage

| Potential Concern | Strategy |
| --- | --- |
| Device labelling/identification | Devices will be stored as per dentures in storage container specifically for the MyoMunchee, labelled with the participants identification number.  The MyoMunchee will be stored as per Maroba Aged Care protocol for storage and identification of usual oral hygiene products |
| Lost/misplaced device | In the event of the MyoMunchee being misplaced/lost a new replacement device will be provided |

1. **Data monitoring for safety**

Data monitoring will occur throughout the study for the safety of residents undergoing the intervention by way of:

- Pre and post intervention assessment
- During intervention with daily monitoring of completion of the trial intervention and completion of data sheets by care staff
- Weekly collection of data sheets to ensure no adverse events

Monitoring and reporting of adverse events (AE), serious adverse events (SAE) and unexpected events (UE) will be conducted as per Maroba Aged Care incident reporting system ‘ionMY’ (governance, risk management, compliance platform), and entered by care staff as per Maroba Aged Care incident reporting guidelines. Events will be reported to the principal investigator within 24 hours of the UE/AE/SAE and entered into the University of Newcastle adverse events form in Research Information Management System within 72 hours of being reported as per NHMRC (2016) guidelines.

All UE/AE/SAE will be:

- assessed by the principal investigator using the University of Newcastle risk assessment matrix and NHMRC (2016) guidelines of level of severity

Grading system for AE

| **Level of severity** | **Criteria of level of severity** |
| --- | --- |
| Mild | Requires minimal/no treatment and do not interfere with daily activities |
| Moderate | Results in low level inconvenience or concern. May cause some interference with function |
| Severe | Interrupts usual daily activity and may require other treatment |

- Reported to the sponsor and trial site by the principal investigator within 24 hours of the principal investigator becoming aware of any urgent safety concerns

Discontinuation of intervention for a participant may occur if:

- There is an AE or medical condition that occurs such that participation in the study would not be in the best interest of the participant
- The participant met an exclusion criterion (newly developed of not identified on consent) that precludes further study participation

Care staff who have concerns that a participant is no longer suitable to continue the intervention will be able to contact the principal investigator both during work hours and after hours via phone/email provided.

1. **Protocol Deviations**

Acknowledgment of the completion of twice daily intervention with the MyoMunchee will be confirmed by care staff via a checklist provided. The checklist will be collected by care staff at the end of each intervention week and replaced with a new intervention checklist with instructions for the intervention for that week.

Deviations from the study protocol such as the use of the device or adherence of the participant or the study site staff will be addressed by the principal investigator. The principal investigator will use continuous vigilance to identify and report deviations within 72 hours of identification of the protocol deviation.

1. **Unexpected or Serious Adverse Events**

The study procedures are not greater than minimal risk, and serious adverse events (SAE) are not expected.

- AE’s are those resulting in any untoward medical occurrence as a result of the intervention
- SAE’s are those resulting in death, life threatening AE’s, requiring hospitalization, or significant disruption of ability to conduct normal functions
- UE’s are those incidents/experiences that warrant consideration of change to the intervention protocol for the safety and welfare of the participant (National Health and Medical Research Council (2016).

The principal investigator will use continuous vigilance to identify and report adverse events within 72 hours of identification of the event to all approving relevant parties.

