# DATA ANALYSIS

**a. Quantitative**

Statistical analyses will be performed using SPSS, version 22. The primary outcome will be reported as numbers and percentages.

Secondary outcome measures will be summarised using mean (SD) for normally distributed data, median (interquartile range) for non-normally distributed data and number (percent for categorical data).

Pre- to post-treatment comparisons will be performed using a paired t-test. Effect size and 95% confidence interval will be reported. The significance level will be set at p<0.05.

In addition, for each of the secondary outcome measures, linear regression will be used to measure changes in secondary variables while controlling for age, cognition, adherence, comorbidities, and ability to implement the MyoMunchee independently.

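### Stopping the device is not kept apart from leaving the study, so residents who stop for harm or intolerance are not assured a post-treatment assessment and the pre-post comparisons may be selective

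*Protocol*

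**What the plan says.** - **Timing of the post measures** (Protocol, Study Procedures, Study procedures, residents): "Following the five week trial of intervention, post-treatment outcome measures will be taken by the lead researcher from the University of Newcastle". The text describes no assessment at early stopping and no follow-up after it.
- **Stopping rule** (Data monitoring for safety): the lead-in is "Discontinuation of intervention for a participant may occur if". The first criterion is "There is an AE or medical condition that occurs such that participation in the study would not be in the best interest of the participant". A second covers an exclusion criterion "that precludes further study participation".
- **Foreseen tolerability problems** (Safety considerations, risk table): coughing leads to a speech pathology review of swallowing "and appropriateness for continuation in study". Oral discomfort leads to a review after which "recommendations will be made for continuation in the study".
- **Safety monitoring** (Data monitoring for safety): the first of three listed methods is "Pre and post intervention assessment".
- **Analysis** (Data Analysis, a. Quantitative): "Pre- to post-treatment comparisons will be performed using a paired t-test". A linear regression of change follows, adjusted for adherence and other covariates.
- **Resident survey**: Study Outcomes, Qualitative gives it to everyone enrolled. Methods of data collection gives it to those who complete the intervention.

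**The concern.** Coughing and oral discomfort are closely related to what the secondary outcomes measure, namely swallowing and oral health. If residents who stop for these reasons also leave the study, the remaining pre-post pairs come from people who tolerated the device. Everyone receives the device and there is no control arm, so nothing offsets that selection. Adjusting for adherence cannot restore a resident who has no post value.

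Three things are at stake:

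- **Efficacy.** It is part of the stated aim, and the pre-post change is the only evidence on it.
- **The next trial.** The study is meant to inform the sample size of a randomised trial. Required size varies with the inverse square of the assumed effect, so an inflated change would make that trial too small.
- **Safety.** The post assessment is named as a safety-monitoring method, yet residents stopped for a safety reason are not assured of having it.

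This is a question of which data are collected. No analysis plan can recover values that were never measured.

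**Working it through.** **1. Text check.** The places that bear on a resident who stops early are:

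| Place in protocol | What is being stopped or decided |
|---|---|
| Stopping rule, lead-in | The intervention (permissive) |
| Stopping rule, criterion 1 | Being in the study |
| Stopping rule, criterion 2 | Being in the study |
| Coughing review | Continuing in the study |
| Discomfort review | Continuing in the study |
| Post measures | After the five-week intervention; nothing on early stoppers |

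Four statements refer to the study and one to the intervention. None describes stopping the device while remaining under assessment. Non-completion is expected, because completion is itself a primary feasibility outcome. The two survey populations also disagree, so the protocol has not settled whether stoppers are followed.

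**2. Who is analysed.** A paired difference needs both values, and so does a regression on change. The analysed set is residents with both assessments.

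**3. Size, as illustration.** The protocol gives no dropout rate, SD or expected effect, so there is no stated figure to reproduce. From the protocol: a recruitment ceiling of 50 residents and a 0.05 significance level. Assumed: a two-sided test, all 50 enrolled, a share d without a post value (0.10, 0.20, 0.30), and a mean change in those residents g worse than in the rest (0.5 or 1.0, in SDs of change).

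Let m be the mean change among those measured, with benefit positive. Then:

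- All-enrolled mean = (1 − d)·m + d·(m − g) = m − d·g, so the overstatement is d·g.
- Pairs left: n = 50(1 − d).
- 95% CI half-width = t(0.975, n − 1)/√n.
- If the all-enrolled mean is zero, m = d·g and the noncentrality is d·g·√n. For d = 0.20 and g = 1.0 this is 0.20 × √40 = 1.26. The rejection probability comes from the noncentral t distribution.

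| d | n | Overstatement, g = 0.5 to 1.0 | Rejection probability if true mean is 0 | CI half-width |
|---|---|---|---|---|
| 0.10 | 45 | 0.05 to 0.10 SD | 0.06 to 0.10 | 0.30 SD |
| 0.20 | 40 | 0.10 to 0.20 SD | 0.10 to 0.24 | 0.32 SD |
| 0.30 | 35 | 0.15 to 0.30 SD | 0.14 to 0.41 | 0.34 SD |

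With few stoppers the bias is small against the sampling error. At 30% with a full SD gap it is nearly as large as the half-width, and a nominal 5% test rejects about 41% of the time.

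**The case against.** A reader might infer that residents who stop have no post value and that every pre-post result is restricted to completers. The protocol does not say so, and the case against that reading is good:

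- The post-measure sentence can be read as a calendar time point. Similar wording is used for the staff questionnaire, where it can only mean study timing.
- The stopping rule is headed as ending the intervention and is permissive. Its criteria use study participation as the test for stopping; they do not say that assessment ends. Withdrawal from the study is covered separately under Ethical Considerations, Vulnerable populations.
- Poorly adherent residents who stay would be measured, and the adherence covariate presupposes that. The analysed set is therefore wider than treatment completers.
- Safety does not rest on the post assessment alone. There is daily monitoring, weekly sheet collection and 24-hour reporting to the principal investigator, and coughing or discomfort prompts an individual review.
- The affected outcomes are secondary, in a feasibility study whose primary outcomes count early stopping openly.
- A flow diagram appears to be missing from the text at hand and may treat early stopping.

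All of this stands against the strong reading. It does not remove the gap. The favourable reading is one a site would have to supply for itself, since four statements point towards leaving the study and none says that a resident who stops is still measured.

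**Conclusion.** The point holds in a limited form. The protocol runs together stopping the device and leaving the study, and it does not assure a post assessment to residents who stop for harm or intolerance. The pre-post comparisons risk being limited to residents who remain. A bias towards benefit is plausible, not proven.

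The size depends wholly on the assumed stopping rate and gap: 0.05 to 0.30 SD over the ranges above. An OHAT example can look more dramatic. If those who remain improve by 1.0 point and stoppers worsen by 1.0, the all-enrolled mean improvement is 0.8, 0.6 or 0.4 at 10%, 20% or 30% stopping, so 1.0 overstates it by 25%, 67% or 150%. Those percentages follow from the assumed reversal and are illustration only; the absolute gap is 0.2 to 0.6 points on a 16-point scale.

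Consent, completion and adherence outcomes are unaffected. Safety information from stoppers is reduced, not absent, because adverse event reporting continues. The change is worth making because it is cheap and the missing values cannot be recovered later.

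**What to change.** 1. In Safety considerations and Data monitoring for safety, word stopping the device separately from leaving the study.
2. In Study procedures (residents), schedule the post measures at five weeks from device start for every resident with baseline measures who has not withdrawn consent, whether or not the device was stopped. The treating team should decide which measures are suitable for a resident who has stopped.
3. Report how many residents lack post values, and why.
4. Reconcile Study Outcomes, Qualitative with Methods of data collection on which residents are surveyed.

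The cost is a wording change and up to about 60 minutes of an already planned assessment, by the same assessor, for each resident who stops. Some will decline, and the reported change may look less favourable. Nothing here alters who stops the device or when.
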